#### Exploratory cost-effectiveness evaluation

A specified economic component will evaluate the feasibility of collecting data on resource use, health and non-health-related benefits. More specifically, it will check the completeness and the ability to obtain data on quality of life using the EuroQol 5-Dimension Questionnaire and healthcare use from patients in the target population to allow estimation of healthcare costs.^41^ Information on resource use will be obtained at 3 months and 6 months and combined with reference prices to measure the total healthcare costs for the intervention and control groups. The costs of medications will be estimated afterward based on the average national drug cost.

### Data collection and management

#### Quantitative data

Three quantitative data collection points are planned: baseline, 3 months, and 6 months (end of the study). The types of data collected, and the timeline are summarised in table 1.

All data will be collected by one member of the research team, or by a study nurse/job student trained by the research team, at the site of the NH. Data on NHRs will be collected from the medical record and also directly from residents, using questionnaires. Proxy data will be collected from relatives of residents with dementia. Because all questionnaires do not have a version available for relatives, fewer data will be collected on residents with dementia (see table 1 for details). Additionally, we will collect implementation data from intervention logs, and from questionnaires completed by HCPs and NHs study coordinators. For HCPs questionnaire, in all participating NH, the NH study coordinator will recruit four to seven HCPs. At minimum, we will ask for the coordinating physician, another GP and two nurses to participate. These HCPs will give oral consent for participation.

All collected quantitative data will be collected and managed using REDCap electronic data capture tools hosted at UCLouvain.^42 43^ REDCap (Research Electronic Data Capture) is a secure, web-based software platform designed to support data capture for research studies.

#### Qualitative data

Qualitative data will be collected by a trained psychologist, at the end of the study, through interviews with HCPs and NHRs from the intervention group. We will aim at interviewing two NHRs and four HCPs of each intervention NH. Purposive sampling will be used to ensure a good diversity representation of residents and HCPs included in the study. As an example, we plan on including residents with a long or short history of BZRA intake, and residents with and without successful deprescribing. Cognitively impaired NHRs unable to take part in a 45 min interview will not be eligible, but their relative could be interviewed if relevant. Eligible HCPs will be approached by our research team and NHRs by HCPs to ask whether they would be willing to take part in a one-to-one 45 min interview. NHRs participating in the qualitative study will have to provide a specific written informed consent. HCPs will provide oral consent.

### Statistical analysis

Quantitative data will be reported using descriptive statistics. Categorical variables will be expressed as numbers and percentages and continuous variables as mean±SD or median (P25–P75) depending on normality assessment. Χ^2^ test (or Fisher’s exact test), Student’s t-test or Mann-Whitney test will be performed to assess differences between intervention and control group regarding patients’ characteristics. Assessments will not be blinded. This feasibility study will not be powered to assess the effectiveness of the intervention. BZRA cessation at 6 months as well as BZRA dose reduction will be reported in each group, but no statistical evaluation will be performed on any primary or secondary outcome measure. Lost to follow-up patients or withdrawn patients will be classified with patients that would have failed BZRA deprescribing.

All qualitative interview transcripts will be entered into QSR NVivo V.11 for data analysis. Inductive and deductive thematic analysis will be used to analyse transcripts content. Interviews will mainly be coded into the TDF domains explored in the interview guides. However, new themes or subthemes may be identified inductively from the data. Two coders will individually analyse the first two interviews for NHRs and for HCPs. They will meet to compare their coding. If satisfying agreement is reached, the remaining interviews will be coded by a single coder. If not, another two interviews will be coded by both coders independently, and coding will again be compared. The above-mentioned method will be used until reaching satisfying agreement, ensuring results reliability and validity.

Missing data will inform the research team of the feasibility of data collection. Hence, the relevance of some variables that would have too many missing values will be discussed prior a potential full implementation trial.

Regarding the health-economic evaluation, provided that the feasibility of the needed data collection is validated, we will conduct an exploratory cost-effectiveness analysis on completed cases following the recommendations of the Belgian Healthcare Knowledge Centre.^44^ The combination of answers to EuroQol 5-Dimension will lead to a health profile of five digits that will be converted into a utility using standard Belgian tariff values.^45^ It will estimate patients’ quality-adjusted life years (QALYs) and associated costs. Given the findings from the analysis, we will conduct a value of information analysis to determine whether future research is worthwhile to assess cost-effectiveness.^46^ We will also calculate the incremental cost per QALY gain to deprescribing BZRA at 6 months compared with usual care by dividing the average difference in cost by the average difference in QALYs to generate the incremental cost-effectiveness ratio (ICER). The ICER represents the additional cost per one unit of outcome gained and indicates the trade-off between total cost and effectiveness when choosing between deprescribing BZRA and usual care.^41^

All quantitative analyses will be performed using R software (‘R Foundation for Statistical Computing, Vienna, Austria’).

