### Study design, setting and participants

We will conduct a cluster-randomised, parallel-group, open-label controlled trial, with NHs being the clusters. As this feasibility study does not aim at evaluating the effectiveness of the END-IT NH intervention for BZRA deprescribing, sample size calculation was not computed. Six NHs will be included. In each of these NHs, 10–15 NHRs will be included. The study will take place between July 2023 and March 2024.

Four of the six NHs will be randomised to the intervention group, and two to the control group. The higher number of NHs in the intervention group will help inform our primary research objective, which is evaluating the feasibility of implementing the END-IT NH intervention. Randomisation of NHs will be performed after the recruitment of NHRs and baseline data collection. Because of the small number of clusters, randomisation will not be stratified. The randomisation will be computerised and done through Research Electronic Data Capture (REDCap). This step will be performed by a member of the research team involved neither in the recruitment nor in the data collection. Because of the nature of the intervention, blinding will not be feasible.

An overview of the study design and timeline is available in online supplemental appendix 3.

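### Resident characteristics are to be compared between arms with tests that assume independent residents, although six whole nursing homes (4 vs 2) are randomised after baseline: a minor correction to the baseline table

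*Protocol article*

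**What the plan says.** The Study design, setting and participants section of the Protocol article fixes the design: "We will conduct a cluster-randomised, parallel-group, open-label controlled trial, with NHs being the clusters". It continues: "Four of the six NHs will be randomised to the intervention group, and two to the control group". On size: "In each of these NHs, 10–15 NHRs will be included". On the method of allocation: "Because of the small number of clusters, randomisation will not be stratified". On timing: "Randomisation of NHs will be performed after the recruitment of NHRs and baseline data collection". There is no power basis for any comparison; the section states that a "sample size calculation was not computed".

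The Statistical analysis section lists the chi-square test, with Fisher's exact test as its alternative, and Student's t-test, and says that one of these or a "Mann-Whitney test will be performed to assess differences between intervention and control group regarding" the patients' characteristics. The same section says that BZRA cessation and dose reduction will be reported per group and rules out statistical testing of primary and secondary outcomes. It does not mention clustering, an ICC, a design effect or an analysis at home level.

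**The concern.** The unit of allocation is the home and the unit of the named tests is the resident. The Recruitment process section says the six homes were chosen to differ in ownership, rural or urban location and presence of an Alzheimer unit. Some similarity among residents of one home, for example in dementia status or dependency, is therefore plausible. The variance of an arm mean is then larger than the tests assume, and their p-values are too small on average.

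A second fault needs no assumption about the ICC. Homes are randomised after baseline data are in, so chance allocation of homes is the known source of any baseline difference between arms. A test of whether the difference arose by chance has nothing to decide.

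These would be the only between-arm hypothesis tests the article specifies. They would stand beside cessation, quality-of-life and cost figures by arm and could lead a reader to call the arms comparable or not comparable on a wrong basis.

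**Working it through.** **Inputs from the Protocol article.** Six homes, 4 vs 2; m = 10 to 15 residents per home, hence 60 to 90 residents in all (40-60 vs 20-30); tests as named in the Statistical analysis section.

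**Assumptions not in the article.** Two-sided 5% level; equal home sizes; ICC from 0 to 0.20; 40% prevalence for the binary example. The article states no size, power or ICC, so there is no figure of its own to reproduce.

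**Step 1: design effect.** DE = 1 + (m − 1) × ICC.
- m = 10, ICC 0.05: 1 + 9 × 0.05 = 1.45.
- m = 15, ICC 0.05: 1 + 14 × 0.05 = 1.70.
- m = 10, ICC 0.20: 1 + 9 × 0.20 = 2.80.
- m = 15, ICC 0.20: 1 + 14 × 0.20 = 3.80.

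**Step 2: approximate actual size of a nominal 5% test.** Size = 2 × [1 − Φ(1.96/√DE)]. At DE 1.45 this is 10.4%; at 1.70, 13.3%; at 2.80, 24.1%; at 3.80, 31.5%.

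**Step 3: simulation with no true difference between arms.** 40,000 runs per setting (8,000 for Mann-Whitney). Rejection rates in %:

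| ICC | t, m=10 | t, m=15 | Mann-Whitney, m=10 | Mann-Whitney, m=15 | chi-square, m=10 | chi-square, m=15 |
|---|---|---|---|---|---|---|
| 0 | 5.0 | 5.0 | 5.1 | 4.6 | 5.2 | 5.2 |
| 0.01 | 6.0 | 6.7 | 5.8 | 6.4 | 6.0 | 6.2 |
| 0.05 | 10.5 | 13.6 | 10.2 | 13.5 | 8.6 | 10.5 |
| 0.10 | 15.8 | 21.3 | 14.9 | 20.2 | 12.3 | 16.0 |
| 0.20 | 25.2 | 33.1 | 24.3 | 31.2 | 19.1 | 25.0 |

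For the t-test, formula and simulation agree closely. The binary variable was made by cutting a normal variable at a threshold, so its ICC label refers to the underlying variable. The correlation on the binary scale is smaller, which helps explain the lower chi-square figures.

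**Step 4: what a home-level analysis would give.** A t-test on the six home means (4 degrees of freedom) rejected in 4.8% to 5.1% of runs at every ICC tried. An exact permutation test has C(6,2) = 15 possible allocations, so its smallest attainable p-value is 1/15 = 0.067.

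**The case against.** The strongest reply is that nothing hangs on these p-values. The study is a feasibility trial, outcomes are described and not tested, and the Discussion says there are no predefined progression criteria. The p-values would sit beside full descriptive summaries. That reply stands, and it sets the weight of the point. It does not make the named tests right for the design.

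The inflation also depends on ICCs that the article does not give. It is slight at 0.01 and lower for the categorical example. Table 1 notes that the insomnia, anxiety and attitude questionnaires are not collected in residents with dementia, so homes contribute fewer residents, and the design effect is smaller, for those variables. This stands too, and is why a range is given.

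The sentence speaks of patients' characteristics and does not say baseline. Baseline is the natural reading, because outcome tests are excluded.

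A reader might infer more than the article supports:
- *That no valid test could ever reach 5% with 4 vs 2 homes.* The 1/15 floor belongs to the exact permutation test only. A t-test on home means keeps its size and can reject.
- *That a false flag is almost certain across many characteristics.* With 10 independent characteristics, the nominal chance of at least one is already 1 − 0.95^10 = 40% from ordinary multiplicity. Independence is implausible, since dependency status, dementia and quality of life are likely to be related.
- *That residents of a home share prescribers.* The article does not say so; the Data collection section asks each home for the coordinating physician and another general practitioner.
- *That these tests will steer outcome conclusions or the covariates of a later trial.* The article ties them to neither.

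**Conclusion.** The point holds as a mismatch between a stated method and the stated design. It is not a detail left to an unseen analysis plan, because the tests are named. With 10 to 15 residents per home, the actual size of a nominal 5% t-test is about 6-7% at ICC 0.01, 10-14% at 0.05, 16-21% at 0.10 and 25-33% at 0.20, and somewhat lower in the chi-square example. If the ICC were zero the size would be right, but the tests would still answer no useful question, since homes are allocated after baseline.

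A flagged difference may still be a real difference between the particular homes drawn into each arm. What is wrong is the p-value as a measure of chance under allocation of homes. The effect is confined to the baseline comparison and to how readers judge comparability, so this is a minor correction and no obstacle to the study or its main results.

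**What to change.** In the Statistical analysis section, delete the sentence on between-group tests. State instead that residents' characteristics will be described by arm and by home, using the summaries the section already names (numbers and percentages, mean and SD, or median and quartiles), without p-values.

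This needs no new data. It removes the testing step and adds only a breakdown by home. The Trial status section says that six-month data collection is still under way, so the change can be made before the analysis. Covariate adjustment of between-arm figures is not needed to correct this point.

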### Intervention

NH allocated to the intervention group will implement the END-IT NH intervention. The six intervention components are summarised in figure 1 and described below. A more detailed description is available elsewhere.^31^

Process and goals setting: NHs direction and HCPs will be asked to define steps in BZRA deprescribing, and to set goals reachable at the level of their NH. For this purpose, we developed a list of possible steps and goals. This tool has been developed to be operationalised at the level of the NH, meaning that each NH can adapt the steps, add steps, appoint a person responsible for them and a timeline.HCPs education: We will provide material for HCPs training in a PowerPoint format. This training encompasses information about BZRA side effects and deprescribing process. Additionally, it prompts HCPs to reflect on the pros and cons of deprescribing, and on case vignettes. The training session will be organised at the level of each NH, preferably by the CP, whose role includes staff training.Physical environment adaptation: We will provide NHs with a list of possible adaptations to promote relaxation and sleep, and each NH will be able to choose what adaptations are feasible in their specific context. This tool allows NHs to appoint responsible staff for adaptations and due date. Adaptations beyond those listed in the document are also possible.Audit and feedback: At the beginning of the intervention and every 3 months, we will provide NHs with feedback data on BZRA use in their NH. This feedback will be based on the percentage of residents taking at least one BZRA (ATC codes N05CD, N05CF, N05BA or N03AE01), as reported by the NH pharmacist. This percentage will be compared with the percentage of NHRs taking at least one BZRA in a previous study conducted in 54 Belgian NHs.^1 2^NHRs and their relatives’ awareness: We will provide an educational leaflet, adapted from the EMPOWER brochure, which has already been shown to be effective in BZRA deprescribing.^35 36^ The adaptation for the Belgian and NH context was performed with the involvement of appropriate stakeholders (HCPs, older adults, NHR) (Pétein *et al*^37^).^31^ This leaflet encompasses information about BZRA side effects, non-pharmacological alternatives for sleep issues and anxiety, a testimony of an NHR and an example of an 18-week tapering scheme. NH staff and/or GPs will be in charge of distributing the leaflet to NHRs and/or relatives. NH staff may choose how and when to use this brochure depending on their specific context. For example, the brochure may be used to introduce deprescribing with the NHR, or HCPs may choose to distribute the brochure to all NHRs they think might benefit from it. In the context of residents with dementia, it is expected that relatives will be more involved.Multidisciplinary work: Our intervention will promote multidisciplinary review of BZRA indications and opportunities for deprescribing. We developed a multidisciplinary opinion document to enable communication between NH staff and GPs, if GPs do not attend multidisciplinary meetings. This tool enables NH staff to report potential BZRA side effects to the GP, and to suggest changes in prescriptions or non-pharmacological approaches. The GP can respond on the same document. As for other intervention components, the NH will have flexibility in how they organise the multidisciplinary meetings and use the multidisciplinary opinion document.

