#### Feasibility of the study design

The feasibility of the study design will be evaluated through four aspects detailed below. First, while recruiting residents, NHs will be asked to record the age and sex of approached residents, and whether the patient agrees, disagrees or gives no answer regarding potential participation in the trial. These records will allow the estimation of the recruitment rate and of differences between participants and non-participants. NHs will also have to evaluate the necessary time for recruitment. Second, the retention of participants will be assessed at each of the data collection points. We will record the number of study withdrawals along with the reasons for withdrawal, patients lost to follow-up and deaths. Third, data will be collected in both study arms as they would be in a full implementation trial in order to assess the rate of missing data. Finally, we will also ask NHs study coordinators to complete a satisfaction survey, regarding the study process. This survey has been adapted from Smailes *et al*.^40^

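### Counting every lost or withdrawn resident as failed deprescribing can override BZRA status known from the medical record, and the rule does not place deaths (minor)

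*Protocol article*

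**What the plan says.** The Statistical analysis section of the protocol article gives one rule for residents who leave the study: "Lost to follow-up patients or withdrawn patients will be classified with patients that would have failed BZRA deprescribing". In the same paragraph it describes the outcome concerned: "BZRA cessation at 6 months as well as BZRA dose reduction will be reported in each group, but no statistical evaluation will be performed". It adds: "This feasibility study will not be powered to assess the effectiveness of the intervention".

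Two other places bear on this rule:

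- Table 1 lists medication use, including BZRA, with the medical record as its source at baseline, 3 and 6 months. Unlike several questionnaires, this row does not carry the footnote that excludes residents with dementia.
- The section on feasibility of the study design says that the team will record withdrawals with their reasons, and also "patients lost to follow-up and deaths". Table 1 lists loss to follow-up as a feasibility measure of its own.

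**The concern.** Three features of the rule fit poorly with the rest of the plan.

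- **Known status can be overwritten.** BZRA use does not depend on the resident answering questions. A resident whose record shows that the drug was stopped by 3 months, and who then withdraws, is a failure under the rule as written.
- **Attrition and response share one class.** The study sets out to measure both. A resident who left without any deprescribing attempt, one who tried and failed, and one who had already stopped all end up in the same category.
- **Deaths have no place.** The design section names three kinds of exit: withdrawal, loss and death. The analysis rule names two. Two analysts could code a death differently and both claim to follow the plan.

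At stake is how the descriptive 6-month rates will be read. The Discussion says that the results will guide the decision whether to proceed, and that there are no predefined progression criteria. The figures will therefore be weighed by judgement, so what is inside each one should be visible.

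**Working it through.** The article states no expected 6-month rate and no attrition rate, and says that a "sample size calculation was not computed". There is no figure to reproduce; what follows shows only how the rule behaves.

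**Inputs from the article**

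- Arm sizes: "In each of these NHs, 10–15 NHRs will be included"; "Four of the six NHs will be randomised to the intervention group, and two to the control group". Intervention: 4 × 10 to 4 × 15 = 40 to 60 residents. Control: 2 × 10 to 2 × 15 = 20 to 30.
- Deprescribing rates of 27% to 80% in earlier, mainly outpatient, studies (Introduction). They serve only to span a range.

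**Assumptions (not in the article)**

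- Attrition d of 10%, 20% or 30%.
- A control success rate of 10%.
- In steps 2 and 3, dropouts succeed as often as residents who are followed.

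**Step 1: direction.** Let p be the success rate among those followed, q the rate among those who leave, and d the proportion who leave.

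- True rate = p(1 − d) + qd
- Reported rate = p(1 − d)
- Shift = −qd

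Within an arm the shift is never upward. It is zero if q = 0, and at most d in size if q = 1.

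**Step 2: one arm, q = p**

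| p | d | Reported p(1 − d) | Shift (points) | Rate if all dropouts succeeded, p(1 − d) + d |
|---|---|---|---|---|
| 27% | 10% | 24.3% | −2.7 | 34.3% |
| 27% | 20% | 21.6% | −5.4 | 41.6% |
| 27% | 30% | 18.9% | −8.1 | 48.9% |
| 80% | 10% | 72% | −8 | 82% |
| 80% | 20% | 64% | −16 | 84% |
| 80% | 30% | 56% | −24 | 86% |

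**Step 3: contrast between arms.** Assume true rates of 27% and 10%, a difference of 17 points.

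| Attrition, intervention / control | Reported rates | Difference (points) |
|---|---|---|
| 10% / 10% | 24.3% − 9.0% | 15.3 |
| 20% / 20% | 21.6% − 8.0% | 13.6 |
| 30% / 30% | 18.9% − 7.0% | 11.9 |
| 30% / 10% | 18.9% − 9.0% | 9.9 |
| 10% / 30% | 24.3% − 7.0% | 17.3 |

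Equal attrition shrinks the contrast. Unequal attrition can shrink it further or push it slightly above the true value.

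**Step 4: in residents.** Take an intervention arm of 60 with 20% attrition: 12 leave and 48 are followed. At 27%, 13 of the 48 have stopped.

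- Among those followed: 13/48 = 27.1%.
- Under the rule: 13/60 = 21.7%.
- If the records showed that 3 of the 12 had stopped (27% of 12 is about 3): 16/60 = 26.7%.

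One reclassified resident moves the intervention rate by 1/60 to 1/40 = 1.7 to 2.5 points, and the control rate by 1/30 to 1/20 = 3.3 to 5.0 points.

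**Step 5: deaths.** Take the same arm with 10% exits, all of them deaths: 6 die, 54 remain, 15 have stopped. Counting deaths as failures gives 15/60 = 25.0%; leaving them out gives 15/54 = 27.8%. The article does not say which applies.

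**The case against.** The case for leaving the rule alone is substantial.

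- Missing-as-failure is a common, conservative convention for cessation outcomes. It keeps every randomised resident in the denominator and is exact if those who leave did not stop or reduce. This stands, and it means the rates can be biased, not that they are.
- The information is kept. Withdrawals with reasons, losses and deaths are recorded, so rates with and without dropouts can be rebuilt. This also stands: the weakness is in classification and presentation, not in data capture.
- Residents who merely tire of questionnaires are not clearly caught. The Discussion provides for shortened data collection so that they stay in the study. This narrows the group affected. Whether records may be read after a true withdrawal depends on consent terms that are not shown.
- Where deaths go is a coding detail that a condensed article may leave to a fuller document. Alone it would not merit a point. It belongs here because the explicit rule covers two of the three exits that the plan itself lists.
- The arms are small and nothing is tested. With about 50 and 25 residents at 30%, the standard error of the difference is √(0.21/50 + 0.21/25) = 11 points before clustering, so most of the shifts in the contrast above are within noise.

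A reader might infer more than the document supports:

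- **That these rates will set the full trial's sample size, so that attrition is charged twice.** The article never says this. It says that the results as a whole, with advisory board input, inform the decision to proceed.
- **That a resident still tapering at 6 months has no category.** Dose reduction is reported beside cessation, and Table 1 counts it as success. The leaflet's "an example of an 18-week tapering scheme" is an illustration, not a study schedule.
- **That failure has no meaning for a lost control.** It means neither stopped nor reduced, and both outcomes are reported in each arm.
- **That the known-status rate should replace the planned one.** It conditions on survival and retention, and overstates success if dropouts failed. Which figure leads is debatable.

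**Conclusion.** The point holds as a minor one. The rule as written can discard a BZRA status that the plan's own data source would supply, merges attrition with non-response in one figure, and does not place deaths.

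Each arm's 6-month rate can therefore be understated, and the descriptive contrast can move in either direction if attrition differs between arms. Conservative describes the rule within an arm, but not for the comparison.

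The size cannot be stated, because the article gives no attrition figure. The understatement of 2.7 to 24 points per arm rests on assumed attrition of 10% to 30%, rates of 27% to 80%, and dropouts succeeding as often as completers. It falls to zero if dropouts truly did not stop or reduce.

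**What to change.** Amend the rule and the results table as follows:

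1. Classify residents who leave by their BZRA status in the medical record, where it is available and consent allows. Impute failure only when status is unknown.
2. Report counts by arm in separate categories: stopped; reduced; unchanged or increased; died; lost or withdrawn with status unknown.
3. Say explicitly how deaths enter each denominator.
4. Show the rate among residents with known status beside the missing-as-failure rate. Neither needs to be named the main figure.

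The cost is one extra rate in the table and a record check for residents who left. No new instrument is needed.
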